### Assessments

All clinical questionnaires will be administered at screening/baseline, at intervention completion (4 weeks), 3 months, and 6 months.

Inclusion of all measures is conditional on approval and/or licensing for the intended purpose.

#### Outcome Measurement Instruments

The GAD-7 is a 7-item self-report scale developed to assess the severity of generalized anxiety disorder symptoms [19]. It is widely used as a brief screening and outcome measure for anxiety in clinical practice and research [20,21]. Measured at baseline, postintervention, and at 3- and 6-month follow-up. Items are scored 0 to 3 (total score 0 to 21). Cutoffs: 5 (mild), 10 (moderate), and 15 (severe). Excellent reliability (Cronbach α≥0.92).

The PHQ-9 is a 9-item self-report instrument designed to assess depressive symptom severity based on *DSM-IV* (*Diagnostic and Statistical Manual of Mental Disorders* [Fourth Edition]) criteria [22]. It is a commonly used tool for depression screening and monitoring treatment outcomes in research and practice [23,24]. Items are scored 0 to 3 (total score 0 to 27). Cutoffs: 5 (mild), 10 (moderate), 15 (moderately severe), and 20 (severe). Measured at baseline, postintervention, and at 3- and 6-month follow-up.

The EQ-5D-5L, developed by the EuroQol Group [25], measures HRQoL across 5 domains (mobility, self-care, usual activities, pain/discomfort, and anxiety/depression) with 5 severity levels. It is extensively used in clinical trials, health economics, and QALY calculations [26]. The Norwegian EQ-5D-5L tariff will be used. Delta QALYs will be calculated using interpolation over the 6-month observation period. The EQ visual analog scale (EQ-VAS; 0-100) captures self-rated health. Utility values for QALY calculation will use the Norwegian EQ-5D-5L value set [27]. Measured at baseline, postintervention, and at 3- and 6-month follow-up.

The Work and Social Adjustment Scale (WSAS) is a 5-item self-report scale developed to measure functional impairment attributable to a specific health problem across work, home management, social and private leisure activities, and relationships [28]. It is frequently used to quantify disability in mental health research and evaluate treatment impact. Scores range from 0 to 40; higher scores indicate greater impairment. A score >20 indicates moderately severe or worse impairment. Measured at baseline, postintervention, and at 3- and 6-month follow-up.

The Client Satisfaction Questionnaire-8 (CSQ-8) is an 8-item self-report tool assessing client satisfaction with health and mental health services. It is widely applied in service evaluation and clinical trials to measure acceptability and perceived benefit of interventions [29]. Administered at postintervention follow-up only.

The System Usability Scale (SUS) [30] is a 10-item Likert-scale questionnaire providing composite app usability score (0-100). The SUS has become an industry standard for app assessment [31]. Administered at postintervention follow-up only.

#### Primary Outcomes

The co-primary outcomes in the trial are (1) the difference in the GAD-7 score for anxiety symptoms between baseline and postintervention for participants with mild to moderately severe self-reported problems with anxiety at baseline (GAD-7 score ≥5), and the difference in the PHQ-9 score for symptoms of depression between baseline and postintervention for participants with mild to moderately severe self-reported problems with depression at baseline (PHQ-9 score ≥5).

#### Secondary Outcomes

The secondary outcomes are (1) change in anxiety symptoms measured by the GAD-7 between baseline and 3 months and 6 months in participants reporting problems at baseline (GAD-7 ≥ 5), (2) change in levels of depressive symptoms as measured using the PHQ-9 for between baseline and 3 months and 6 months in patients reporting problems at baseline (PHQ-9 ≥ 5), and (3) QALY accrual as measured using the EQ-5D-5L, and (4) change in functional impairment as measured using the WSAS.

#### Other Assessments

Other assessments include (1) client satisfaction following completion of the app using the CSQ-8 at postintervention (tertiary outcome); (2) the SUS (tertiary outcome); (3) app engagement metrics (sessions completed, time spent, features used; automatically recorded; tertiary outcome); (4) self-reported use of health services (for use in calculation of costs and as a tertiary outcome); and (5) use of concurrent psychological treatments assessed at each follow-up time point with type and frequency of any concurrent treatment recorded and included as covariates in sensitivity analyses.

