### Interventions

#### Overview

No medication is administered within the study, nor are any medications prohibited.

Participants are also prohibited from using other self-help mental health smartphone apps during the 4-week intervention period. Adherence to this rule will be assessed at each follow-up time point via a dedicated question in the app. Concomitant psychological therapy is prohibited during the 4-week intervention period but is permitted during the 3- and 6-month follow-up phases; its use will be recorded as a potential covariate in sensitivity analyses.

Tankevirus and Grubl are 2 structurally similar self-help apps with different visual design, different lengths, and different contents. Shared characteristics include:

Onboarding with baseline measurement of mental health with feedbackPsychoeducational videosA set of shorter videos and tasks delivered 1 each day following the introductory videosMental health measurement following completion, with feedback on self-reported changeLong-term follow-up measurement at 3 and 6 monthsAutomatic reminders (daily push notifications)Program progress trackingOptions to rewatch elements of particular interest

The regular versions of Tankevirus and Grubl use a set of standardized questionnaires used to track mental health, specifically the Patient Health Questionnaire-4 (PHQ-4) inventory, which comprises 2 questions from the PHQ-9, covering depression, and 2 questions from the GAD-7, covering anxiety; the Somatic Symptom Scale 8-item (SSS-8); and a visual analogue scale inspired by the one used in the EQ-5D family of instruments. In the MIND-APP implementation, these are substituted by the longer PHQ-9 and GAD-7 instruments, and the full EQ-5D-5L.

The placebo condition will be designed to mimic these structural elements, with the exception of the content elements, as described below

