#### Questions Regarding Current and Past Health Care Use for Mental Health Issues

Participants will be asked whether they have at any point in the past required mental health care of different types, and will be asked to check any in a list of different types of health services they have used in the past, including follow-up from general practitioner; having seen a psychologist or psychiatrist; and having required hospitalization.

Participants will be asked whether they currently receive any mental health support and will be asked to check any that are relevant from a list. Participants will be excluded if they indicate that they are currently being treated for mental health issues or if they indicate that they have previously required hospitalization for mental health issues.

Excluded individuals will be thanked for their interest and informed of the reason for exclusion. Participants indicating severe depression (PHQ-9 ≥20) or responding with a score of ≥2 on PHQ-9 item 9, suggesting suicidal ideation, will also be provided with information on where they can seek help. Draft information to be provided is available in Multimedia Appendix 4. Individuals excluded based on other criteria will be provided with links to public information on mental health and links to the regular Tankevirus and Grubl apps. All excluded individuals will be informed that all the information provided will be deleted once recruitment is complete.

Given the financial incentive provided, there is a risk of individuals attempting duplicate participation. While this cannot fully be ruled out, the risk is limited by use of phone number and full name at registration.

Eligible participants will be asked to complete remaining baseline questionnaires before randomization.

Participants are informed that they will have the option to move on to another treatment option following closure of the data collection.

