### Sample Size Calculation

Sample size calculation assumptions were based on self-reported data from the Tankevirus app in Norway combined with information from 2 meta-analyses of mobile apps for mental health [11,32]. The 2 meta-analyses both indicate high variability both in quality of evidence and estimated effect sizes. Assuming low to moderate effects, we assumed Cohen *d* of 0.3. For a single outcome, targeting 80% power and a critical α of .05, regular power analyses indicate a need for 176 participants in each study arm. However, the coprimary end points of the trial and expected correlation between the GAD-7 and the PHQ-9 imply reduced power.

To better reflect these factors, we built a Monte Carlo simulation based on recorded responses to the PHQ-4, which comprises 2 questions from the GAD-7 and 2 questions from the PHQ-9 collected from the existing Tankevirus app. We assume a correlation of approximately 0.7 between the PHQ-9 and the GAD-7. Assuming a distribution of responses taken from these self-report data, targeting 80% power, with a critical α=.05, the analyses suggested that 300 participants per arm are required for comparisons between each active arm and the placebo condition, given the coprimary end points and the observed proportions having problems with either anxiety or depression but not both.

The trial is powered for separate comparison of each app to placebo, but is not powered to allow meaningful comparison of the outcomes between Tankevirus and Grubl. The recruitment target is 1000 participants to account for attrition.

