### Statistical Analysis Plan

#### Statistical Methods

Observed values from the per-protocol population will be used for the primary analysis. Sensitivity analyses including complete cases and an intention-to-treat analysis with imputed values will also be conducted. The RCT app automatically records all use of all app functions with timestamps, and per-protocol compliance will be determined as having viewed the 3 primary videos of the Tankevirus and Grubl arms or having completed the 3 primary units of the placebo arm. Participants with compliance below the per-protocol threshold will be included in the intention-to-treat analysis but not the per-protocol analysis.

The primary analysis will use an analysis of covariance (ANCOVA) framework: the postintervention score will be the dependent variable, treatment arm the primary factor, and baseline score a covariate. This adjusts for regression to the mean and improves precision. Stratification variables used in randomization (sex, age group, and symptom severity) will also be included as covariates.

The trial compares 2 separate treatments with placebo, and the literature is divided on whether testing should be adjusted for multiplicity [33]. To account for the 2 treatment-vs-placebo comparisons while controlling the familywise type I error rate, Dunnett procedure will be applied to the ANCOVA-adjusted (least squares) means, exploiting the positive correlation between the 2 test statistics arising from the shared placebo arm [34].

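### Sensitivity analyses adjust for psychological treatment that can only vary after randomisation; if the apps change its uptake, the adjusted arm comparison can be biased

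*Protocol article*

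**What the plan says.** All references are to the protocol article.

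- **Other Assessments**, item 5, on concurrent psychological treatment at each follow-up: "type and frequency of any concurrent treatment recorded and included as covariates in sensitivity analyses".
- **Interventions, Overview**, on concomitant therapy, in softer terms: "its use will be recorded as a potential covariate in sensitivity analyses". The same sentence sets the timing: "Concomitant psychological therapy is prohibited during the 4-week intervention period but is permitted during the 3- and 6-month follow-up phases".
- **Questions Regarding Current and Past Health Care Use for Mental Health Issues**: "Participants will be excluded if they indicate that they are currently being treated for mental health issues". The exclusion list in Textbox 1 also names ongoing psychological treatment.
- **Statistical Methods**, on the primary ANCOVA, which also adjusts for baseline score: "Stratification variables used in randomization (sex, age group, and symptom severity) will also be included as covariates". Therapy use is not in that model.
- **Other Assessments**, item 4, makes self-reported health service use a cost input and a tertiary outcome.

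Neither statement of the covariate says which question the adjusted analysis answers, and neither names a method for events after randomisation.

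**The concern.** A covariate fixed before randomisation sharpens the arm comparison without changing what it estimates. A covariate that arises after randomisation may itself be a result of the allocated app. An app that reduces symptoms may leave fewer people looking for therapy; an app that teaches about mental health may lead more people to seek it. In either case the adjusted arm coefficient is no longer the total effect. Reading it as the effect that does not run through therapy would require that no unmeasured factor drives both therapy use and later symptoms, and randomisation does not secure that.

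The stake is how the 3- and 6-month results are read. A sensitivity analysis is meant to show whether a result is robust. This one could differ from the main result, or seem to confirm it, for reasons unrelated to the app.

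**Working it through.** **1. The plan's own yardstick.** Sample Size Calculation assumes d = 0.3, 80% power and alpha .05 (taken as two-sided) and gives 176 per arm for a single outcome. Normal approximation: n = 2(1.960 + 0.842)² / 0.3² = 2 × 7.851 / 0.09 = 174.5, so 175. The t-test solution is 175.38, so 176. The figure reproduces. It serves here only to fix 0.3 SD as the planning effect; no sample size changes.

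**2. When the covariate can vary.**

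| Period | Rule in the plan | Possible variation |
|---|---|---|
| Screening | Current treatment excluded | None by design |
| Intervention, up to 4 weeks | Therapy prohibited | Breaches only |
| 3- and 6-month phases | Therapy permitted | Free to vary |

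So the variable cannot correct a baseline imbalance.

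**3. Why arm could affect it.** Safety Considerations says that users who report symptoms at the severe-depression or suicidal-ideation thresholds during the trial are told where to seek help. That ties symptoms after randomisation, which the apps aim to reduce, to treatment seeking.

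**4. Size.** The documents give no uptake rates, so every uptake input below is an assumption. With A = arm, B = baseline, U = an unmeasured factor, M = post-intervention score, T = therapy started, Y = later score:

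- M = −d·A + 0.5·B + 0.5·U + error (total variance 1 within arm)
- logit P(T = 1) = a + gS·M + gA·A
- Y = −0.3·d·A + 0.7·M + h·T + error (SD 0.714)

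With h = 0 the total effect is −0.3d − 0.7d = −d. Y was regressed on A and B, then on A, B and T, with 1,000,000 participants per scenario. Negative values favour the app.

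| Scenario | Therapy, placebo / app | Without T | With T | Shift |
|---|---|---|---|---|
| d = 0, gA = 0, gS = 1.5, a = −1.1, h = 0 | 31.3% / 31.4% | −0.004 | −0.005 | 0.000 |
| d = 0.3, gA = 0, gS = 0, a = −1.1, h = 0 | 24.9% / 25.0% | −0.300 | −0.300 | 0.000 |
| d = 0.3, gS = 0.5, a = −2.2, h = 0 | 10.9% / 9.6% | −0.299 | −0.296 | +0.003 |
| d = 0.3, gS = 1.0, a = −1.1, h = 0 | 28.6% / 23.5% | −0.301 | −0.277 | +0.024 |
| d = 0.3, gS = 1.5, a = −1.1, h = 0 | 31.4% / 24.8% | −0.297 | −0.257 | +0.040 |
| d = 0.3, gS = 1.5, a = −1.1, h = −0.3 | 31.3% / 24.7% | −0.282 | −0.262 | +0.020 |
| d = 0, gA = +0.7, gS = 1.0, a = −1.5, h = 0 | 22.1% / 34.0% | 0.004 | −0.051 | −0.055 |
| d = 0, gA = −0.7, gS = 1.0, a = −1.5, h = 0 | 22.2% / 13.4% | −0.001 | 0.040 | +0.042 |

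Shifts are taken before rounding.

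- **Arm does not affect uptake:** no shift.
- **App works and uptake follows symptoms:** attenuation of at most 0.040 / 0.297, about 13%.
- **App does nothing to symptoms but changes help-seeking:** a spurious difference of about −0.05 to +0.04 SD. Its sign depends on the direction of the help-seeking effect.

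A second simulation, with 20–30% uptake driven by symptoms and an unmeasured severity factor, gave 3–5% attenuation at d = 0.3. Under no true effect, with help-seeking odds ratios of 1.5–2.0, it gave a spurious benefit of 0.028–0.058 SD (0.028 / 0.3 = 9% to 0.058 / 0.3 = 19% of the planning effect).

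**5. Against sampling error.** With 300 per arm the standard error of a standardised difference is √(2/300) = 0.082. If baseline correlates 0.6 with outcome (assumed), it is 0.082 × √(1 − 0.36) = 0.065. The largest shift, 0.058, is below one standard error.

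**The case against.** The strongest reply is that nothing decisive is touched. The co-primary outcomes are read at post-intervention, when therapy is prohibited, and the primary model omits it. That stands. A reader might infer that the trial's main conclusion is at risk; the documents do not support this.

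A reader might also infer that the adjustment necessarily biases the comparison. It does not: the shift is zero unless arm affects uptake, and the documents do not show that it will. That stands too, so the claim is that it can bias.

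Third, the shift is small and every uptake input is assumed. This stands, and it limits the weight of the point.

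Fourth, adjusting for a co-intervention is a crude attempt at a real question, the effect not running through other therapy. Fair: saying that the estimate answers no question would go too far. The question is unnamed, and the assumptions needed are strong and unstated.

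Fifth, part of the remedy is nearly present. Health service use is a tertiary outcome, co-treatment is recorded at every time point, and nothing in the compliance definition drops a participant for starting therapy. Only a small wording gap remains there, since psychological treatment is not itself named as an outcome.

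Sixth, one statement says only that therapy is a potential covariate, and details may sit in an analysis plan that is not shown. But the other states inclusion outright. That is a stated rule, not an omitted detail.

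**Conclusion.** The point holds as a limited correction to the sensitivity analyses. The plan enters as a regression covariate a variable that, by its own eligibility rules, varies only after allocation. If the apps alter therapy uptake, the adjusted comparison can be biased in either direction. In the scenarios examined the shift runs from zero to about 0.05 SD. That range rests wholly on assumed uptake, symptom dependence and help-seeking effects. It is an illustration and not a bound, because stronger unmeasured shared causes would enlarge it. Confidence is high on the principle and low on the size. The primary ANCOVA is unaffected. The exposure is mainly at 3 and 6 months, and at post-intervention only through breaches of the prohibition.

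**What to change.** 1. In Other Assessments and in Interventions, Overview, delete concurrent psychological treatment as a regression covariate, so that the two sections agree.
2. Report its use by arm at each time point as an outcome.
3. State that the main 3- and 6-month estimates use scores regardless of therapy use.
4. If the effect without added therapy is of interest, name it as a separate hypothetical estimand. One suitable method is to set scores to missing from the first follow-up at which therapy is reported, and multiply impute them from baseline and earlier scores.
5. State the missing-at-random assumption behind that imputation, and that unmeasured severity can leave residual bias. In a simulation with no true effect, an unmeasured severity factor and help-seeking odds ratios of 1.5–2.0, covariate adjustment gave −0.029 to −0.053 SD and imputation −0.007 to −0.017 SD. About a quarter (0.007 / 0.029) to a third (0.017 / 0.053) of the artefact remained.

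The cost is wording and, if item 4 is taken up, one extra imputation analysis that rests on an untestable assumption. No new data are needed, recruitment has not begun, and the rules on when therapy is allowed stay as they are.

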### Participant Pathway

The participant pathway is summarized in Figure 4. Potential participants will be guided to a trial website or directly to the iOS/Android MIND-APP app.

**Figure 4 figure4:**
[figure not shown]
Flowchart showing the patient pathway from recruitment to final follow-up. All timings are measured from the timing of the first “dose,” that is, the first main video of the Tankevirus and Grubl arms or the first main element of the placebo arm. GAD-7: Generalized Anxiety Disorder-7; PHQ-9: Patient Health Questionnaire-9.

Once MIND-APP is installed, participants will be asked to read the provided trial information, after which they will be asked to provide consent by providing their name, age, and phone number. To complete registration, they will be sent an SMS text message with a 1-time code that they enter in the app. As described in the section “Data Management and Protection,” the name and phone number will be stored separately from all other trial data and will be used for the following purposes:

To ascertain that all participants are real personsTo verify identity and prevent duplicate registrations

Participants provide their full name and mobile phone number during the registration process. This information is transmitted via HTTPS through the encrypted app backend and stored in a separate database from all trial data. It is used solely for identity verification and compliance with accounting regulations for voucher distribution and is deleted upon completion of data collection.

Participants may request withdrawal and deletion of their data at any point up to the formal end of the trial. After this point, data will have been deidentified and merged into the locked analysis dataset; individual-level deletion will no longer be possible.

The formal end of the trial is defined as the date of the last participant’s last data capture (6-month follow-up assessment).

Following data collection cutoff, all participants are offered access to the 2 active intervention apps (Tankevirus and Grubl).

Financial compensation consists of NOK 500 (approximately US $50), to be provided either as a one-off upon completion of the 6-month follow up or in 2 tranches of NOK 250 (approximately US $25) at completion of the primary follow-up and the 6-month follow-up. As financial compensation can function as a disincentive for some potential participants, all participants will be offered the option to donate to a set of charitable causes as an alternative to receiving gift cards. For participants eligible to receive compensation in the form of gift card vouchers, the name and phone number will be transferred to the Akershus University accounting department to comply with accounting regulations.

A temporary key will be used to tie participant trial data to the name and phone number to allow provision of gift cards at the end of the trial. This link will be deleted as soon as the gift cards have been issued and the trial is completed or as soon as the potential participant is identified as ineligible.

Participants will be informed that they have the option to withdraw from the trial and request deletion of any registered data up until the first event resulting in deletion of the link between the registered phone number and the corresponding trial data, which will occur once they have completed the 6-month follow-up or once 7 months have elapsed since the first use of the app.

